## Abstract

**Background:**

Two million people in the UK are living with or beyond cancer and a third of them report poor quality of life (QoL) due to problems such as fatigue, fear of cancer recurrence, and concerns about returning to work. We aimed to develop and evaluate an intervention based on acceptance and commitment therapy (ACT), suited to address the concerns of cancer survivors and in improving their QoL. We also recognise the importance of exercise and vocational activity on QoL and therefore will integrate options for physical activity and return to work/vocational support, thus ACT Plus (+).

**Methods:**

We will conduct a multi-centre, pragmatic, theory driven, randomised controlled trial. We will assess whether ACT+ including usual aftercare (intervention) is more effective and cost-effective than usual aftercare alone (control). The primary outcome is QoL of participants living with or beyond cancer measured using the Functional Assessment of Cancer Therapy: General scale (FACT-G) at 52 weeks. We will recruit 344 participants identified from secondary care sites who have completed hospital-based treatment for cancer with curative intent, with low QoL (determined by the FACT-G) and randomise with an allocation ratio of 1:1 to the intervention or control. The intervention (ACT+) will be delivered by NHS Talking Therapies, specialist services, and cancer charities. The intervention consists of up to eight sessions at weekly or fortnightly intervals using different modalities of delivery to suit individual needs, i.e. face-to-face sessions, over the phone or skype.

**Discussion:**

To date, there have been no robust trials reporting both clinical and cost-effectiveness of an ACT based intervention for people with low QoL after curative cancer treatment in the UK. We will provide high quality evidence of the effectiveness and cost-effectiveness of adding ACT+ to usual aftercare provided by the NHS. If shown to be effective and cost-effective then commissioners, providers and cancer charities will know how to improve QoL in cancer survivors and their families.

**Trial registration:**

ISRCTN: ISRCTN67900293. Registered on 09 December 2019.

All items from the World Health Organization Trial Registration Data Set for this protocol can be found in Additional file 2 Table S1.

**Supplementary Information:**

The online version contains supplementary material available at 10.1186/s13063-024-08062-4.

## Introduction

### Background and rationale

Some two million people in the UK are living with or beyond cancer (also described as cancer ‘survivors’ and adopted for brevity in this paper) [1]. The number is increasing [2], with 50% of all those newly diagnosed now living for at least 10 years [3]. By 2028, an extra 55,000 people each year will survive for 5 years or more following their cancer diagnosis [4]. About a third have poor quality of life (QoL) and even more report other distress [5–7]. A national survey assessing the QoL of 3300 adult cancer survivors reported key issues or concerns including: fear of recurrence (57%), fatigue (43%), body image concerns (31%), and lack of exercise (30%) [5]. Poor QoL is also associated with unemployment in those of working age [8], with up to a third losing their work after cancer diagnosis [5]. The NHS Cancer Quality of Life survey in April 2023 reported that amongst over 100,000 patients who have had their cancer diagnosis for longer than 18 months, 80% across all age groups report a problem with an aspect of their health. This includes anxiety and depression (52%), pain and discomfort (64%), and problems with usual activities (52%) [9]. There is wide variation in NHS ‘aftercare’ [6, 10], and interventions to improve QoL and address the unmet needs of patients are only moderately effective, and often unavailable [10, 11].

Two key policy documents have highlighted the importance of cancer survivorship [6, 7]; the National Cancer Survivorship Initiative included goals to reduce the proportion of people with unmet physical and psychological support needs and to increase the proportion of cancer survivors able to work [6]. The report recommended self-management, after appropriate assessment and treatment, and both physical activity programmes and vocational support [6]. The goals of the Independent Cancer Taskforce, established by NHS England, included every person with cancer having access to a ‘recovery package’ of aftercare with ‘stratified pathways of follow-up care (7)’. Some recommendations focused on the need for more research into survivorship issues and QoL, including return to work [7]. Other recommendations covered the need for rehabilitation services and specific treatment for depression [7]. The need for evidence-based interventions to facilitate a return to a normal life in those living with and beyond cancer is also increasingly being recognised by the professions [12, 13].

In attempting to address the problems that cancer survivors face, non-pharmacological interventions such as cognitive behavioural therapy (CBT), exercise, and mindfulness-based stress reduction (MBSR) have shown to be effective at improving overall QoL, mostly in the short term [11]. In addition, only exercise and CBT consistently showed efficacy, although the effect sizes were small to moderate, with limited long-term follow-up [11]. A recent systematic review of an ACT intervention (and interventions based on the principles of ACT) in adult cancer survivors highlights ACT as an effective intervention to address the issues concerning cancer survivors but recommended more robust studies [14]. In a trial using ACT in 135 cancer survivors, the intervention was delivered in group sessions by community social workers trained in ACT. The trial demonstrated accelerated psychological recovery and energy levels with the intervention [15]. There have also been a few small trials in cancer patients who were in active treatment [16], but no large trials of ACT in cancer survivors looking at QoL, where the intervention is delivered to participants one-to-one by trained therapists [11, 14].

Acceptance and commitment therapy (ACT) lends itself to addressing the aforementioned problems in cancer survivors. ACT is a ‘third wave’ psychological intervention that was purportedly developed following questions some researchers had over the validity and effectiveness of cognitive restructuring in cognitive behavioural therapy (CBT) versus behavioural interventions, for the treatment of depression [17]. CBT identifies thoughts that cause distress, and alternative perspectives are then explored if and when appropriate [16]. In contrast to CBT, third-wave approaches (like ACT) are not concerned with challenging the content/frequency of negative thoughts and emotions. ACT aims to increase psychological flexibility, which in this context, refers to the ability to adapt to demands, shift perspectives, and balance competing desires and needs through processes involving acceptance, mindfulness, commitment, and values-based behaviour change [14].

Overall, an ACT intervention which is person-centred, and integrated with both an exercise intervention [18] and work support—when appropriate to the individual’s life goals [19], is therefore appropriate in addressing the needs of those living with and beyond cancer [16, 20]. As we are integrating ACT with options to support work/vocational activity and exercise, we are therefore calling this integrated approach ‘ACT Plus (+)’. An evaluation of the effectiveness, and economic outcomes of an intervention found to be promising in cancer survivors, would be an important contribution to the NHS [10, 11]

Here, we describe how we will evaluate the effectiveness and cost-effectiveness of our ACT+ intervention.

### Aims and objectives

The aim is to evaluate whether ACT+ in addition to usual aftercare is more effective and cost-effective than usual aftercare alone in improving QoL in people living with and beyond cancer and experiencing low QoL. The specific objectives are as follows:To conduct a randomised, controlled trial to examine the effectiveness of ACT+ in addition to usual care compared to usual care alone on clinical outcomes at 52-week follow-upTo determine the cost-effectiveness of ACT+ with usual care versus usual care alone in terms of quality-adjusted life years (QALYs)To determine the mechanism of treatment, via the investigation of hypothesised mediatorsTo determine variations in treatment effect by participant characteristics, via the exploration of potential moderators

### Trial design

This is a multi-centre, parallel group, theoretically driven, pragmatic, randomised controlled, superiority trial including an internal pilot. We will also undertake a health economic evaluation and a process evaluation with a formal investigation of hypothesised mediators. The primary outcome will be the Functional Assessment of Cancer Therapy: General scale (FACT-G) at 52-week follow-up. The unit of randomisation is the individual study participant performed as block randomisation with a 1:1 allocation ratio. Patients living with cancer and carers including those from an ethnically diverse background are involved in the design and implementation of the trial to improve the relevance and overall quality of the research.

### Methods: participants, interventions, and outcomes

#### Study setting and participants

Participants will be recruited from secondary care settings within five London NHS Trusts and one NHS Trust in Sheffield, specifically from the cancer follow-up clinics associated with our cancer groups of interest.

The ACT+ intervention will be delivered by participating therapists from NHS Talking Therapies (formerly known as Improving Access to Psychological Therapies, IAPT), specialist psychological therapy services, or cancer charities providing counselling or psychological therapies. NHS Talking Therapy sites are selected based upon their geographical proximity to the patient populations attending the recruiting sites.

The full list of recruitment and intervention sites is available from the authors.

#### Eligibility criteria

Eligible participants must have attended, or are being followed up by, a participating cancer clinic and must be within 24 months of having completed cancer treatment with curative intent or be in long term remission (where applicable). Eligible participants must also be considered to have low QoL as determined by a score of 78 or less (out of a maximum score of 108 and a minimum of 0) on the Functional Assessment of Cancer Therapy – General (FACT-G) [21, 22]. A full list of inclusion and exclusion criteria are provided in Table 1.

**Table 1 Tab1:** Inclusion and exclusion criteria

Inclusion criteria	Exclusion criteria
Patients within 24 months of having completed cancer treatment of the index cancer (or about to complete) with curative intent/long term remission for: breast cancer, lower gastrointestinal cancer, a urological cancer, a haematological cancer, head and neck cancer, and any other common cancer with good survival Aged 18 years or over Ability to give informed consent Sufficient fluency in spoken English to be able to participate in a talking-based therapy delivered in English With a score of 78 or less on the Functional Assessment of Cancer Therapy – General (FACT-G)	Will not have completed their cancer treatment by the commencement of the trial (excepting those receiving long-term, ongoing maintenance treatment, e.g. androgen suppression therapy in prostate cancer) Receiving treatment for symptom control alone Currently receiving another psychological intervention (NB participants taking. antidepressants or anxiolytic drugs remain eligible) Other serious co-morbid condition which would make it difficult for the participant to receive a talking-based one-to-one intervention Require urgent psychiatric or clinical psychology assessment

#### Recruitment

Identification of potentially eligible participants will be carried out by the site NHS clinical team and study research assistants. Interested potential participants will be asked three screening questions. This is done using a 5-point Likert scale, where a score of 1 is poor, and 5 is excellent. The three questions are as follows: How would you rate your physical health? How would you rate your feelings of wellbeing? How would you rate your quality of life? For those whose score indicates they may require support (a score of 10 or lower) a member of the research team will, with their permission, administer the FACT-G. Those participants who score 78 or less on the FACT-G and remain interested in the study will be sent the baseline questionnaire along with the informed consent form by a study research assistant. Participants will need to return both or complete them online using a secure data entry system, before joining the study. On return of the baseline questionnaire, the research assistant will check to see if the participant remains eligible on the FACT–G score criterion. Thus, only participants whose FACT-G QoL scores have been below 79 on two separate occasions, typically separated by about a week, will be eligible to join the study, and randomised to either receive the intervention or usual care only.

#### Additional consent provisions for collection and use of participant data and biological specimens

Participants will have the option on the ICF to give their consent to be approached for participation in a separate interview study. The protocol for the interview study can be found: https://openresearch.nihr.ac.uk/articles/3-24. Participants also provide their consent to be included in a 2-year follow-up if they have been in the study for 2 years by the time of last participant, last 52-week follow-up.

#### Intervention

ACT is an intervention that aims to increase psychological flexibility. Psychological flexibility refers to an individual’s ability to adapt to demands, shift perspectives, and balance competing desires and needs [16, 23–25]. This means that ACT could help a patient to accept what cannot be changed (e.g. that the cancer might recur), while committing themselves to the things they can change (i.e. meeting their goals in life, irrespective of having had cancer).

We developed the intervention to be integrated with options for work/vocational activity support and exercise in ways that are tailored to each participant’s personal values and goals, and therefore called this ‘ACT Plus (+)’. We also developed a participant handbook and manuals for therapists. The process of developing and refining the ACT+ intervention will be reported separately elsewhere (in preparation).

The intervention is delivered by therapists who had undergone specifically designed training in ACT+ led by the senior study therapist (co-chief investigator TC). Full details of the SURECAN ACT+ training and its evaluation have been published [26]. The core professions of the therapists include clinical psychologists, high intensity therapists (from NHS Talking Therapies), cognitive behaviour therapists trained in ACT, and trained counsellors. Treatment integrity will be assessed at the end of the trial guided by Perepletchikova et al.’s treatment integrity procedures checklist [27].

The sessions can be delivered face-to-face (at the therapist’s main practice), by phone or via online video calls, according to participant preference. The intervention involves up to eight sessions delivered at weekly or fortnightly intervals. Sessions last around 1 h and include homework to be completed prior to the next session. All sessions should take place within a range of 14–20 weeks from a participant being allocated to the intervention arm at randomisation (depending on the frequency of sessions, i.e. weekly or fortnightly, and allowing occasions for missed/rescheduled sessions). Participants are also provided with the ACT+ participant handbook. Eligible participants randomised to the intervention arm will receive the ACT+ intervention in addition to usual aftercare.

#### Explanation for choice of comparators

Since we wish to know whether the addition of ACT+ is effective and cost-effective compared to usual aftercare, it is necessary to make the comparison arm treatment as usually provided by the NHS. Allowing a usual care control arm also solves the problem of offering a standardised usual aftercare intervention, which would likely duplicate what patients already receive (see below). However, we will enhance the control by providing the Macmillan Cancer Support leaflet, signposting the participant to aftercare available.

Usual after-care varies across different cancer groups even within the same trust as our development work demonstrated [10]. A national survey of oncology health care practitioners, undertaken as part of our programme development work in 2015 (prior to the COVID-19 pandemic), showed that specific interventions that were offered by the NHS included the following: dietary advice (72%), a medical assessment (69%), exercise advice (65%), a one off ‘end of care’ assessment (62%), and counselling (61%). Interventions such as CBT (16%), mindfulness (21%), and return to work support (20%) were infrequently offered [10].

#### Criteria for discontinuing or modifying allocated interventions

Intervention arm participants may discontinue receiving the intervention at any point they request.

#### Strategies to improve adherence to interventions and assessment of compliance

The therapists undergo monthly drop-in supervision sessions which are conducted by TC. The supervision sessions promote quality of therapy and adherence to the study therapy and protocol. Individual advice and support for therapists is also available as required.

#### Outcomes

##### The primary outcome

The primary outcome will be the total score of the Functional Assessment of Cancer Therapy: General scale (FACT-G) at 52 weeks follow-up; FACT-G is a generic measure of physical, social, emotional, and functional QoL; it ranges from 0 to 108 with a higher score indicating a better QoL [21]. The method of aggregation will be the mean FACT-G score at 52 weeks for both arms. In the programme grant development work comparing different quality of life measures related to cancer, the FACT-G was found to address their concerns and was the easiest to complete [28].

##### Secondary outcomes

The secondary outcomes and mediator measures shown below (unless specified) will be reported at all timepoints: baseline, 7 weeks, 16 weeks, 52 weeks, and 2 years (where applicable). The method of aggregation will be mean scores for both arms. Further details will be presented in the forthcoming statistical analysis plan.The total score of the FACT-G at all other timepointsThe FACT-G sub-scale total scores (physical well-being [range 0–28], social/family well-being [range 0–28], emotional well-being [range 0–24] and functional well-being [range 0–28]. With higher scores indicating better QoLFear of cancer recurrence [29]. Four question self-report scaleThe Impact of Cancer scale (IOCv2): positive and negative impacts subscales [30]Anxiety and depression, measured using the Hospital Anxiety and Depression Scale (HADS) [31]The Chalder Fatigue Scale (CFQ) [32] which is composed of 11 items, each of which is answered using a 4-point Likert scale ranging from 0 (less than usual) to 3 (much more than usual). The maximum score is therefore 33, and a higher score is associated with a worse health stateMeasuring independent physical activity (frequency of occurrences, and duration in minutes) using an modified version of the Godin leisure score index questionnaire [33]The EuroQol (EQ-5D-5L) [34] will be used to measure health-related QoL and to derive quality-adjusted life years (QALYs). The EQ-5D-5L consists of five domains (mobility, usual activities, self-care, pain/discomfort, and anxiety/depression). Each domain is scored between 1 (no problems) and 5 (extreme problems)Health and social care utilisation and use of informal care measured using an adapted version of the Client Service Receipt Inventory [35]. This will cover the three months before randomisation and the periods up to 16-week and 52-week follow-up. The CSRI will be self-completed by participants. We will also collect employment statusEngagement and frequency of engagement in any new meaningful activities (e.g. new work, job, hobbies, or interests) at 16- and 52-week follow-up. This will be analysed as a categorical variable and therefore represented as a descriptive table, for each arm

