### Sample size

A total sample size of 266 (133 per arm) would provide 90% power to detect a minimally clinically important effect size (Cohen’s *D*) of 0.4 assuming a 2-sided 5% significance level. The effect size is based on existing literature, determined previously as 0.42 and 0.46 for FACT-G [40, 41]. This effect size represents a difference of 6 points on FACT-G in a cancer population [22]. Assuming each therapist sees 10 participants, an intracluster correlation coefficient (ICC) of 0.01, and allowing for drop-out by 52 weeks of 15%, the estimated total sample size required is 344 (172 per arm) patients to be recruited over 33 months. This represents an average of 10.4 participants per month in total across participating sites. Based on the numbers of patients seen in three sites (845 per annum), this sample size can be achieved assuming a recruitment rate of at least 20% of eligible participants. The sample size assuming independent observations was calculated using the power command in Stata. This was then manually multiplied by the design effect and divided by the proportion expected at follow-up to account for loss to follow-up.

Average estimates of therapist effects for RCTs have been shown to be 0.08, however they are highly variable across studies due to their dependence on the specific outcomes, research design and statistical analysis used [42, 43]. ACT+ uses a manualised approach with structured intervention sessions, and therapists receive training and monthly supervision on its delivery. End of treatment is scheduled for 16 weeks, while the primary outcome of FACT-G score is collected at 52 weeks. These features are likely to reduce therapist effects to negligible levels at the point of primary outcome collection. However, to be conservative we have allowed for the presence of low levels of clustering, estimated at 0.01.

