### Statistical methods

#### Statistical methods for primary and secondary outcomes

Prior to any analysis taking place, a statistical analysis plan will be developed and made publicly available, containing a more detailed and technical description of the analysis to be performed. To ensure transparency and reproducibility, its content will follow the guidelines proposed by Gamble et al. [47].

The analysis will be reported in line with the CONSORT guidelines and the extension for non-pharmacologic treatment interventions [48]. Baseline demographic and clinical outcomes will be summarised by treatment group. Normally distributed data will be summarised by mean (standard deviation); non-normally distributed data will be presented as median (interquartile range) and categorical variables presented as *n* (%).

The analysis will follow intention-to-treat principles, where participants with available data are included in the treatment group to which they were randomised. Hypothesis tests will be two-sided and estimated treatment effects will be accompanied by a 95% confidence interval. For all analyses, a significance level of 5% will be used.

The primary analysis will be a mixed effects linear regression of the total FACT-G score at 52 weeks with a random effect for therapist, fixed effects for baseline score, and randomisation stratification factors. Secondary outcomes will be modelled similarly.

To explore the treatment effects over time, the analysis will be repeated with multilevel mixed effects models with a nested structure to include an additional random effect for individual, a fixed effect for time, and an interaction between treatment and time. Safety data will be summarised by treatment group.

Predictors of costs and cost-effectiveness will also be identified, the latter being calculated as the monetary value of QALYs minus therapy costs. Generalised or standard linear models will be used as appropriate.

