## Discussion

The common concerns for cancer survivors include fear of cancer recurrence, fatigue, body image concerns, lack of exercise, and unemployment in those of working age. These concerns may be associated with a poor quality of life (QoL). There is a clear need to support the increasing numbers of cancer survivors in the UK and beyond and a need for robust evidence-based studies assessing the effectiveness of aftercare available to them. The SURECAN study aims to address this need by identifying those cancer survivors with low QoL who are often receiving inadequate aftercare following their cancer treatment and offer them an intervention known as acceptance and commitment therapy (plus) (ACT+) to investigate if it improves their QoL. This intervention is suited to such patients to aid improvement in their health and well-being after cancer. To our knowledge, this is the first time an intervention based on ACT that integrates options for physical exercise and work/vocational activities support has been developed and evaluated in a large study for its effectiveness in addressing the specific needs and concerns of cancer survivors.

The COVID-19 pandemic caused much disruption to the running of cancer services and reduced communication and contact between cancer patients and their clinicians. SURECAN recruitment was therefore adapted to encompass recruiting patients either face-to-face in clinic or remotely (as described in the ‘Recruitment’ section). The intervention can be delivered online or over the phone, and training of therapists can also be delivered online.

This trial will provide us with evidence determining if there is an improvement in QoL while being cost-effective of ACT+ compared with usual aftercare. We will also determine if ACT+ reduces any anxiety and depression and helps participants manage the fear of the cancer coming back and if there is more engagement with activities that are meaningful to the participant.

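### New meaningful activity is confined to a descriptive table because it is categorical, although the Discussion says the trial will determine whether engagement is greater

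*Protocol article*

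**What the plan says.** Three places in the protocol article bear on this outcome.

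- **Secondary outcomes.** The last item in the list is engagement, and frequency of engagement, in new meaningful activities such as work, hobbies or interests, at 16 and 52 weeks. Its analysis is stated as: "This will be analysed as a categorical variable and therefore represented as a descriptive table, for each arm". The opening of the same section sets mean scores by arm as the default summary and adds: "Further details will be presented in the forthcoming statistical analysis plan".
- **Statistical methods for primary and secondary outcomes.** "The primary analysis will be a mixed effects linear regression of the total FACT-G score at 52 weeks", with a therapist random effect and fixed effects for the baseline score and the stratification factors. Then: "Secondary outcomes will be modelled similarly". The section also sets a general reporting rule: "Hypothesis tests will be two-sided and estimated treatment effects will be accompanied by a 95% confidence interval".
- **Discussion.** One sentence begins "We will also determine if ACT+ reduces any anxiety and depression", goes on to fear of recurrence, and ends with "if there is more engagement with activities that are meaningful to the participant".

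**The concern.** The reason given for stopping at a table does not support that choice. A categorical outcome can be compared between arms with an adjusted effect and an interval by standard methods.

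The Discussion puts meaningful activity beside anxiety, depression and fear of recurrence, as things the trial will settle. Those are scale scores that the general modelling rule covers. Meaningful activity has its own sentence, which sends it elsewhere.

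What is at stake is how the result gets reported. With only counts per arm, the authors would either read a difference off raw percentages without its uncertainty, or be unable to answer the question they raised. The outcome also bears on the vocational component that the intervention adds to ACT, so readers are likely to look for it.

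**Working it through.** **1. The passages side by side**

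| Section | What it implies for this outcome |
|---|---|
| Secondary outcomes | Analysed as categorical, shown as a table by arm; no contrast, interval or test named |
| Statistical methods | Secondary outcomes modelled like the primary, by a linear mixed model with the baseline score as covariate |
| Discussion | The trial will determine whether engagement is greater |

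The general modelling rule does not fill the gap. It refers to a linear model for a score, and this item is categorical. It also adjusts for a baseline value, and this item is listed only at 16 and 52 weeks. The one analysis statement specific to the outcome is the table.

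**2. The plan's own sample size, checked first**

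The Sample size section says 266 in total "would provide 90% power to detect a minimally clinically important effect size (Cohen’s *D*) of 0.4 assuming a 2-sided 5% significance level".

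- The two-sample t calculation with d = 0.4, two-sided 5% and 90% power gives 132.3, so 133 per arm and 266 in total. This matches.
- Design effect: 1 + (10 − 1) × 0.01 = 1.09.
- Inflated total: 266 × 1.09 / 0.85 = 341.1, so 342 against the stated 344. This is close enough, and no number is in dispute.

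**3. Would a between-arm estimate be informative at this size?**

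Inputs from the protocol: 172 per arm and 15% drop-out, so 172 × 0.85 = 146.2 analysed per arm.

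Assumption: the protocol gives no rate for new meaningful activity, so control rates p0 of 20%, 30%, 40% and 50% were tried, with differences of 10, 15 and 20 points.

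Half-width of the 95% CI for a risk difference: 1.96 × √{[p0(1 − p0) + p1(1 − p1)] / n}.

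- p0 = 0.20, p1 = 0.30: 1.96 × √[(0.16 + 0.21) / 146.2] = 0.099.
- p0 = 0.40, p1 = 0.50: 1.96 × √[(0.24 + 0.25) / 146.2] = 0.113.
- Second case with n divided by 1.09: 0.118.

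Over the whole grid the half-width is about 10 to 12 points.

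Power over the same grid:

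| True difference | No clustering | Design effect 1.09, both arms |
|---|---|---|
| 10 points | 40–51% | 38–47% |
| 15 points | 73–82% | 69–79% |
| 20 points | 93–97% | 91–95% |

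Difference detectable with 80% power at an assumed 50% rate:

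- (1.96 + 0.842) × √(2 × 0.25 / 146) = 0.164, about 16 points.
- Multiplied by √1.09 = 1.044: 0.171, about 17 points.

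**4. What a table alone hides**

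Suppose the table showed 40% against 50%. The 10-point gap would look like more engagement, but its interval is 10 ± 11.3, that is about −1 to 21 points. That would not settle the question in the Discussion, and the table alone would not show it.

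**The case against.** The strongest reply is that the disputed sentence concerns display only. The section sets mean scores as the default summary, means do not suit a categorical item, and so a table is substituted. On that reading the general modelling rule still applies, and the model is one of the details left to the statistical analysis plan. This is possible but strained. The sentence says how the outcome will be analysed as well as how it will be shown, and it gives the categorical scale as the reason for a table. The modelling rule that would have to apply is linear. The protocol has stated a rule here, so this is more than a detail left open.

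Other parts of the reply stand and limit the point:

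- The Discussion sentence is not one of the objectives listed under Aims and objectives, and no power is attached to it. Softening that sentence would be a sufficient remedy.
- The outcome is any new meaningful activity, including hobbies and interests. A reader might infer that the effect on return to work goes unanswered. The document does not support that, because employment status is collected separately.
- A reader might also infer that the trial will certainly produce no treatment effect for this outcome. That goes too far, because the analysis plan is not shown and could add a model, although it would then depart from the protocol's own sentence.
- The response format is not described, so ordered frequency categories cannot be taken for granted.

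**Conclusion.** The point holds as a minor inconsistency in one secondary outcome. The protocol limits new meaningful activity to a table by arm for a reason that does not justify it, the Discussion promises a comparative answer, and the general model does not suit the item. These three statements should be reconciled.

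An estimate would be worth having at the planned size: large differences would be found, while a difference of about 10 points would probably be left uncertain. The figures rest on assumed control rates, on 15% drop-out, and on independent observations or a design effect of 1.09. That design effect uses the intracluster correlation assumed for FACT-G. Applying it to both arms is cautious, because the therapist effect arises from delivery of ACT+. The primary analysis and the sample size are not touched.

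**What to change.** In Secondary outcomes, replace the table-only sentence with a statement to this effect:

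- Engagement (yes/no) at 16 and 52 weeks will be compared between arms by logistic regression, with the stratification factors and the therapist term used in the primary model. An odds ratio and a risk difference will be reported, each with a 95% CI.
- Frequency of engagement will be compared by ordinal regression if its categories are ordered.
- The table by arm is kept as a supplement.

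In Statistical methods, say that the linear model applies to score outcomes and that this item follows the rule above.

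If the team prefers to keep this outcome descriptive, reword the Discussion sentence so that it promises description only.

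The cost is up to two extra models per time point, so up to four in all over 16 and 52 weeks, and no new data. The alternative costs one reworded sentence.
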